### **b. Objective**

1. To estimate the absolute risk of recurrent VT in patients with a history of VT who undergo various types of surgery.
2. To identify risk factors for recurrent VT in these patients.

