### **3. Statistical analysis**

#### **a. Methods**

Follow-up time will be calculated from the start of follow-up (i.e. 1. from stop date anticoagulant treatment after first VT and 2. from date of first VT onwards as a sensitivity analysis) until the end of follow-up (end of study, dead, recurrent event or loss to follow-up, whichever occurs first). The time window of surgery exposure for each individual is defined as 3-months from the surgery date. The total follow-up time in which patients are not exposed will be calculated as the total follow-up time minus the exposure time. As a sensitivity analysis, we will vary the time window of exposure because it is not known for how long the VT risk is increased after surgery. Therefore we will also consider a 1-month, 6-month and 1-year time window after surgery. We will calculate cumulative incidences for recurrent venous thrombosis for the exposed time windows and incidence rates by dividing the number of events by person-time for the exposed and the unexposed time periods.

Cox-proportional hazards modeling (with a time-dependent co-variate [surgery]) will be used to calculate a hazard ratio for developing recurrence. Also, we will estimate Hazard Ratios for several types of surgery on recurrence risk, and adjust for important confounders. Absolute risks for

recurrent VT will be calculated for several types of surgery (for all different time windows after exposure).

To identify high risk groups, we will perform a matched case-control study within this cohort. Cases are patients with a recurrent event who underwent surgery, controls are patients without a recurrent event who also underwent surgery. Cases and controls will be matched for [type of] surgery exposure. Four possible risk factors will be tested: 1. The presence of Factor V Leiden or non-O blood type or prothrombin mutation, 2. provoked or unprovoked first event, 3. DVT or PE as a first event and 4. sex. Odds ratios with 95% CIs will be calculated for these risk factors using logistic regression analysis. A prediction model will be developed if the number of cases is sufficient enough.

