**b. Sample size considerations**

4731 patients were followed over time of which 700 developed a recurrence. Because we have no information on the frequency of the exposure, sample size calculations are estimations. If we assume an exposure to surgery of 10% and a 5% recurrent VT rate in the unexposed, we are able to find a relative risk of 1.6, with a power of 80%.

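### Factor V Leiden, prothrombin mutation and non-O blood type are tested only as one any-of factor, so the odds ratio cannot show which trait carries the risk

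*Protocol*

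**What the plan says.** The second objective (Protocol, 1b) is "To identify risk factors for recurrent VT in these patients", that is, in patients with a previous thrombosis who undergo surgery. Section 3a gives the means: "To identify high risk groups, we will perform a matched case-control study within this cohort". It continues "Four possible risk factors will be tested" and lists them. Item 1 is "The presence of Factor V Leiden or non-O blood type or prothrombin mutation". The other three are whether the first event was provoked, whether it was DVT or PE, and sex.

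The count of four holds only if item 1 is a single variable. Three separate traits would make six factors. The analysis is stated as "Odds ratios with 95% CIs will be calculated for these risk factors using logistic regression analysis". A further step is conditional and its contents are open: "A prediction model will be developed if the number of cases is sufficient enough". The table shells in section 4 have no rows for the three traits, separately or together. The protocol gives no reason for combining them, and no frequency or expected effect for any of them.

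**The concern.** Item 1 joins a blood group with two mutations under an or-rule. Three things follow from the definition alone, without any outside figure:

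- The composite is at least as common as its most common part.
- Its odds ratio is an average over whichever combinations of traits the positives carry, so it cannot be assigned to any one trait.
- A patient with two or three traits is classed with a patient who has one.

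The purpose is to find risk factors and high-risk groups. A weak or null composite result could conceal a mutation effect. A clear positive result would not tell a physician whether blood group, Factor V Leiden or the prothrombin mutation matters. Only the second objective is affected; the absolute risks and the surgery hazard ratios are not.

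**Working it through.** **The plan's own figure.** Section 3b states "4731 patients were followed over time of which 700 developed a recurrence" and "If we assume an exposure to surgery of 10% and a 5% recurrent VT rate in the unexposed", with a detectable relative risk of 1.6 at 80% power. With 473 exposed and 4258 unexposed patients and alpha 0.05 (assumed, as none is stated), the detectable relative risk is 1.65 two-sided (power 75.0% at exactly 1.6) and 1.57 one-sided (power 82.6% at 1.6). The stated figure is thus reproduced to rounding. It is used here only to gauge the number of cases: 4731 × 0.10 = 473 exposed, 5% × 1.6 = 8%, and 473 × 0.08 = 37.8, so about 38 cases and 435 controls.

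**Assumptions.** The protocol gives none of these, so they are shown as ranges: non-O prevalence n = 55-75%, Factor V Leiden f = 5-20%, prothrombin mutation p = 2-5%, all independent.

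**Share of patients positive:** C = 1 − (1 − n)(1 − f)(1 − p).
- Lowest: 1 − 0.45 × 0.95 × 0.98 = 0.581.
- Highest: 1 − 0.25 × 0.80 × 0.95 = 0.810.

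**Share of positives through non-O alone:** S = n(1 − f)(1 − p) / C.
- Lowest (n = 0.55, f = 0.20, p = 0.05): 0.418 / 0.658 = 0.635.
- Highest (n = 0.75, f = 0.05, p = 0.02): 0.698 / 0.767 = 0.910.

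**Composite relative risk if carrying a mutation doubles risk.** The reference is patients with none of the traits.
- Non-O has no effect: RR = S × 1 + (1 − S) × 2 = 2 − S, which runs from 2 − 0.910 = 1.09 to 2 − 0.635 = 1.36.
- Non-O also doubles risk, and carrying more than one trait adds nothing further: every positive patient has RR 2, so the composite RR is exactly 2 at every prevalence.
- If effects multiply on the odds scale instead, over slightly wider ranges (non-O 50-75%, prothrombin mutation up to 6%), the composite odds ratio is 1.09-1.44 with non-O null and 2.1-2.5 with an odds ratio of 2 for each trait.

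**Does pooling buy power?** The table gives approximate power, ignoring the matching, with 38 cases, 435 controls and two-sided 0.05. It covers three assumed prevalence sets (non-O / Factor V Leiden / prothrombin): 60/10/3%, 70/15/5% and 70/20/6%.

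| True odds ratios | Three-way composite | Two mutations pooled | Factor V Leiden alone |
|---|---|---|---|
| Non-O 1, mutations 2 | 7-9% | 42-52% | 38-49% |
| Non-O 1, mutations 3 | 14-18% | 79-89% | 74-87% |
| Non-O 2, mutations 2 | 39-50% | 42-52% | 38-49% |

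In the last row the composite beats the two-mutation pool in one of the three sets (50% against 42%) and loses in the other two (39% against 49%, and 39% against 52%). The prothrombin mutation alone has 22-30% power at an odds ratio of 2. With so few expected carriers, that approximation is rough.

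**The case against.** A reader might infer that a factor carried by most patients cannot identify a high-risk group at all. The documents do not support that. The protocol names non-O among its possible risk factors, so a null effect of blood group is not its premise. If non-O does raise risk, the composite shows an association and separates off a lower-risk minority, which is useful for stratification. A majority category is not disqualifying in itself: sex is on the same list, and one sex must make up at least half of the patients. Likewise, dominance by blood group is not a fact that the protocol states; it depends on the assumed prevalences.

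There is also a fair case for pooling. About 38 cases give 38 / 4 = 9.5 per factor with four factors and 38 / 6 = 6.3 with six, if modelled jointly. With no association, a prothrombin prevalence of 2-5% means 38 × 0.02 = 0.8 to 38 × 0.05 = 1.9 carriers among the cases, so that odds ratio would be close to uninformative. Limiting a sparse analysis to four pre-specified tests is a legitimate aim. Where non-O and the mutations all have an odds ratio of 2, neither approach is well powered, and splitting wins clearly only when blood group has no effect.

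Finally, a statistical analysis plan that is not at hand may contain component lines, and nothing in the protocol forbids them. What stands is narrower: the protocol itself fixes the variable as a three-way composite, and that choice limits what the second objective can conclude. The sparsity argument supports pooling the two mutations with each other. It does not support adding blood group to them.

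**Conclusion.** The point holds in a limited form. That the composite odds ratio cannot be attributed to a trait, and that multiple carriers are merged with single carriers, follows from the definition and needs no outside figure.

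The size rests on assumed prevalences and independence. On those assumptions, 58-81% of patients are positive and 64-91% of positives are so through non-O alone. A doubling of risk by the mutations shows as a relative risk of about 1.1-1.4 if blood group has no effect, and as about 2 if blood group doubles risk too. Dilution is therefore possible but not certain, because it depends on an effect that the protocol does not give. This is a cheap improvement to the analysis for the second objective. It is not an error in a stated figure, and it leaves the first objective untouched.

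**What to change.** In section 3a, report an odds ratio for non-O blood type separately from the mutations. Give Factor V Leiden and prothrombin mutation one line each, or pool those two if carriers are too few. Keep the three-way composite as an additional line, and label the component results exploratory. If three separate tests were intended all along, correct the count of four.

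The cost is two or three extra table lines from data that must already exist to form the composite. The drawbacks are one or two added tests and wide intervals for the rarer mutations, above all the prothrombin mutation.

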### **b. Exposure (independent variable)**

We are interested in all surgical procedures (i.e. orthopedic, non-orthopedic, gynecological, urological, abdominal, vascular, neurosurgical, etc), both daycare procedures and operations whereby patients are hospitalized for one or more days (see table under 4b), and we will differentiate between major and non-major surgery. These procedures are identified using ICD-coding that is registered in the CBS database.

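### The risk-factor study matches on type of surgery, but the stated logistic regression makes no provision for the matching; ignoring it would pull the odds ratio for sex toward 1

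*Protocol*

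**What the plan says.** Section 3a of the protocol introduces a second, nested design for the risk-factor objective: "To identify high risk groups, we will perform a matched case-control study within this cohort". The groups are defined as follows: "Cases are patients with a recurrent event who underwent surgery, controls are patients without a recurrent event who also underwent surgery". The matching is then fixed: "Cases and controls will be matched for [type of] surgery exposure".

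Four factors are to be tested. One combines Factor V Leiden, non-O blood type and prothrombin mutation; the others are "provoked or unprovoked first event, 3. DVT or PE as a first event and 4. sex". The analysis sentence is "Odds ratios with 95% CIs will be calculated for these risk factors using logistic regression analysis", and the paragraph ends with "A prediction model will be developed if the number of cases is sufficient enough".

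The surgical categories in section 2b include "orthopedic, non-orthopedic, gynecological, urological, abdominal, vascular, neurosurgical, etc", and the planned tables in section 4 list gynaecological and urological surgery on separate rows. The adjustment variables in section 2d, and in the footnote to the tables in section 4b, are age, sex, BMI and comorbidity. Surgery type is not among them. The matching ratio, the fineness of the surgery categories used for matching, and the choice between individual and frequency matching are not stated.

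**The concern.** Matching makes the distribution of surgery type the same in cases and controls by design. The analysis must then condition on surgery type or include it in the model. If it does neither, the crude odds ratio lies closer to 1 than the within-type odds ratio for any factor whose frequency differs by type of surgery.

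Sex is one of the four factors and is the most exposed. A gynaecological set contains only women and so carries no information on sex, yet it still enters the crude comparison and dilutes it. Urological sets, mostly men, act the same way to a lesser degree. At stake is the size of a named risk factor under Objective 2.

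A related point concerns the conditional prediction model, which follows directly after the matched analysis with no data set named. In a matched set the proportion of cases is set by the matching ratio, and the effect of surgery type on risk has been removed by design.

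**Working it through.** **The plan's own figure.** The protocol gives no figure for the case-control analysis. Its only planning figure (section 3b) is a detectable relative risk of 1.6 for surgery against no surgery in the cohort. With 4731 patients, 10% exposed, 5% recurrence in the unexposed and an assumed two-sided alpha of 0.05, the detectable value at 80% power is 1.65 (1.646, which agrees with 1.6 to one decimal). That figure is not in question here; its inputs are used below only for scale.

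**Formula for the crude odds ratio.** Let surgery type *s* make up share w_s of the cases and, because of the matching, the same share of the controls. Let p_s be the proportion of men among controls of that type, and let OR be the common within-type odds ratio.

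- Proportion of men among cases of type *s*: q_s = OR·p_s / (1 − p_s + OR·p_s)
- Pooled proportions: P = Σ w_s p_s for controls, Q = Σ w_s q_s for cases
- Crude odds ratio = [Q/(1 − Q)] / [P/(1 − P)]

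All shares and sex mixes are assumptions; the protocol gives none. Other surgery is taken as 50% men unless stated.

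| Assumed mix | P | Q at OR 2.0 | Crude OR, true 2.0 | Crude OR, true 3.0 |
|---|---|---|---|---|
| 10% gynaecological | 0.450 | 0.600 | 1.83 | 2.54 |
| 20% gynaecological | 0.400 | 0.533 | 1.71 | 2.25 |
| 10% gynaecological, 10% urological (80% men) | 0.480 | 0.622 | 1.78 | 2.44 |
| 20% gynaecological, 20% urological (90% men) | 0.480 | 0.589 | 1.56 | 1.95 |
| No near-single-sex type, five equal types with 35 to 60% men | 0.440 | 0.605 | 1.95 | 2.89 |

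The fourth row in full: P = 0.2×0 + 0.2×0.9 + 0.6×0.5 = 0.48. In urological surgery the odds of 9 become 18 among cases, so q = 18/19 = 0.947. In other surgery q = 2/3. Q = 0 + 0.2×0.947 + 0.6×0.667 = 0.589. Crude OR = (0.589/0.411)/(0.48/0.52) = 1.56.

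The loss from a true 2.0 is 11% in the third row (1 − 1.78/2) and 22% in the fourth (1 − 1.56/2).

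**A factor weakly related to surgery type.** With an assumed prevalence of 60 to 70% across types, a true 2.0 appears as 1.99 and a true 3.0 as 2.99 (losses of 0.3% and 0.5%). Widening the range to 50 to 70% gives 1.97 for a true 2.0, a loss of 1.3%.

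**Prediction from an unweighted matched set.** The section 3b inputs imply a risk of 5% × 1.6 = 8% in the exposed, that is odds of 0.08/0.92 = 0.087. The sample odds of being a case are 1 at 1:1 matching and 0.25 at 1:4, so they are inflated 1/0.087 = 11.5-fold and 0.25/0.087 = 2.9-fold. Apparent risk would be 50% or 20% whatever the type of surgery.

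**Scale.** The same inputs imply 0.10 × 4731 = 473 exposed patients and 473 × 0.08 = 38 cases.

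**The case against.** Several arguments limit the point, and most of them stand.

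- *The protocol does not say that the regression is unconditional.* True. The term can cover the conditional form or a model with surgery-type terms, and a statistical analysis plan, if one exists, may settle it. A reader might infer that the plan has chosen an analysis that breaks the matching; the text does not go that far. It does fix the matching and name the model while leaving out the link between them, although the same section spells out the form of the Cox model.
- *The fineness of matching is unknown.* Also true. If matching is only on broad groups such as orthopaedic and non-orthopaedic, or major and non-major, no stratum is single-sex and the bias may be small, as the last row of the table suggests (1.95 for a true 2.0).
- *Only sex is shown to be affected.* A reader might infer that all four odds ratios are materially biased. Nothing in the protocol suggests that genotype or blood group, DVT against PE, or provoked status varies strongly by type of surgery.
- *The bias is small beside the sampling error.* With 38 cases, an assumed 1:4 ratio and 50% men among controls, the standard error of the log odds ratio at a true 2.0 is √(1/25.3 + 1/12.7 + 1/76 + 1/76) = 0.38. The shifts in the table at a true 2.0 run up to ln(2/1.56) = 0.25. This is fair as to scale, but it does not justify a bias that costs nothing to remove.
- *The prediction model is not tied to the matched set.* Correct. A reader might infer that the design cannot support such a model. The study is nested in an enumerated cohort, so sampling fractions can be known, and all operated patients are available.

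**Conclusion.** The point holds in a limited form. The protocol matches on type of surgery and names a logistic regression with nothing that accounts for the matching, there or in its adjustment lists. If the matching is ignored, a true odds ratio of 2.0 for sex would appear as about 1.8 to 1.6 when gynaecological and urological surgery each make up an assumed 10 to 20% of cases and controls. The direction of the bias does not depend on those shares; the size does, and it also requires matching fine enough to isolate these types. For factors weakly related to surgery type the loss is about 1% or less.

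A reader might also take this to undermine Objective 1. It does not: the absolute risks by type of surgery come from cumulative incidences in the cohort and do not use the case-control data. Only the risk-factor results under Objective 2, and a prediction model if it were fitted to the matched set without weights, are touched.

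**What to change.** In section 3a, replace the general reference to logistic regression with one of two statements that fits the matching actually used: conditional logistic regression on the matched sets, or, if matching is by frequency, logistic regression with type of surgery as a model term. Name the surgery categories used for matching, so that it is clear which strata carry no information on sex.

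Add one sentence on the prediction model: if it is developed, it will be fitted in all operated patients with type of surgery as a predictor, or to the matched sample weighted by the known sampling fractions. Without one of these, the model gives uncalibrated absolute risks and no surgery-type effect.

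The cost is two or three sentences and a different model call. No new data are needed. Confidence intervals may be slightly wider.

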**b. Sample size considerations**

4731 patients were followed over time of which 700 developed a recurrence. Because we have no information on the frequency of the exposure, sample size calculations are estimations. If we assume an exposure to surgery of 10% and a 5% recurrent VT rate in the unexposed, we are able to find a relative risk of 1.6, with a power of 80%.

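### The 80% power for a relative risk of 1.6 comes from a fixed ever/never-surgery comparison and does not apply to the planned Cox model with a 3-month surgery window

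*Protocol*

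**What the plan says.** Section 3b (Sample size considerations) starts from the cohort: "4731 patients were followed over time of which 700 developed a recurrence". It then assumes that 10% are exposed to surgery and concludes that, with "a 5% recurrent VT rate in the unexposed, we are able to find a relative risk of 1.6, with a power of 80" per cent. Its one caveat is "Because we have no information on the frequency of the exposure, sample size calculations are estimations". The section names no exposure window, person-time, hazard ratio or length of follow-up.

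Section 3a (Methods) defines exposure differently: "The time window of surgery exposure for each individual is defined as 3-months from the surgery date". On the comparison time it says "The total follow-up time in which patients are not exposed will be calculated as the total follow-up time minus the exposure time". The model follows from this: "Cox-proportional hazards modeling (with a time-dependent co-variate [surgery]) will be used to calculate a hazard ratio for developing recurrence".

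**The concern.** The power statement treats surgery as a fixed attribute: a tenth of patients are exposed for their whole follow-up. Under section 3a a patient with one operation contributes a quarter of a year of exposed time, and the rest of that patient's follow-up joins the reference time. Ten per cent of patients exposed is therefore far less than ten per cent of person-time exposed. In a time-dependent model the information on the surgery effect depends mainly on the number of recurrences inside the windows.

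The inputs also sit awkwardly together. The section reports 700 recurrences in 4731 patients and then assumes 5% in the unexposed, without saying over what period. Both counts precede the removal of cancer patients, unlinked patients and uncertain recurrences.

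At stake is how the overall hazard ratio is read. This is the protocol's only power statement, and it credits the study with a good chance of finding a 1.6-fold increase.

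**Working it through.** **Inputs from the protocol.** N = 4731 and 700 recurrences (section 3b); 10% exposed, 5% risk in the unexposed, relative risk 1.6 (section 3b); window 3 months = 0.25 year (section 3a).

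**Assumptions not in the protocol.** Two-sided alpha 0.05; one operation per operated patient; mean follow-up T of 3 to 8 years (section 2a gives only the end, 2008-2009); all 700 recurrences count, which is generous.

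**Step 1: reproduce the stated figure.**
- Groups: 0.10 × 4731 ≈ 473 and 0.90 × 4731 ≈ 4258. Risks: 5% and 1.6 × 5% = 8%. Pooled risk: 0.9 × 0.05 + 0.1 × 0.08 = 0.053.
- Pooled standard error: √(0.053 × 0.947 × (1/473 + 1/4258)) = 0.01086.
- Power with pooled variance throughout: Φ(0.03/0.01086 − 1.96) = 79%; minimum relative risk 1.61.
- Power with pooled null and unpooled alternative variance (standard error 0.01291): Φ((0.03 − 1.96 × 0.01086)/0.01291) = 75%; minimum relative risk 1.65.

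So the stated figure is, within the usual differences between formulas, a fixed two-group comparison of proportions.

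**Step 2: the planned exposure.** Exposed share of person-time: f = 0.10 × 0.25/T. Given D recurrences, the number falling in exposed time is binomial with probability p = f·HR/(1 − f + f·HR). The exact test rejects at k or more exposed events, where k is the smallest count with upper-tail probability at most 0.025 under p = f.

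Worked case, T = 5 and D = 700: f = 0.005, so 3.5 exposed events are expected under no effect, and k = 9. At HR 1.6, p = 0.008/1.003 = 0.00798, or 5.6 expected events, and the chance of 9 or more is 11%.

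| T (years) | f | Exposed events expected, no effect | Power at HR 1.6 (exact) | HR detectable at 80% (exact) | Same, Schoenfeld |
|---|---|---|---|---|---|
| 3 | 0.83% | 5.8 | 22% | 2.6 | 3.2 |
| 5 | 0.50% | 3.5 | 11% | 3.3 | 4.5 |
| 7 | 0.36% | 2.5 | 11% | 3.7 | 5.9 |
| 8 | 0.31% | 2.2 | 14% | 3.6 | 6.7 |

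The exact columns are not quite monotone because the counts are so small. The Schoenfeld column is exp(2.80/√(D·f·(1 − f))); its power at HR 1.6 is 20% at 3 years and 10% at 8. A Wald test on the same counts reaches 33% at 3 years, still far from 80%.

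**Step 3: vary what is unknown (exact method).**
- Events: the protocol's own risks imply 4258 × 0.05 + 473 × 0.08 ≈ 251 recurrences. With 251 events the detectable HR is about 3.9 at 3 years and 5.4 at 5 years.
- Operations: with 30 per 100 patients and 700 events it is about 1.8 at 3 years and 2.1 at 5 years. About 50 per 100 patients and only 3 years' follow-up are needed to reach 1.62.
- Reading 10% as a share of person-time: Schoenfeld gives exp(2.80/√(700 × 0.1 × 0.9)) = 1.42 with 700 events, so 1.6 does not follow on that reading either.

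**Step 4: the recurrence risk.** 700/4731 = 14.8%, against about 251/4731 = 5.3% implied by the assumptions. Linkage of 95% alone (section 2d) takes 700 to about 665; the numbers lost to cancer and to uncertain recurrences are not given.

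**The case against.** The best defence is that section 3b presents its calculation as an estimate because surgery frequency is unknown, and that nothing operational hangs on it. The cohort is already fixed and linked. The objectives (absolute risk and risk factors) are not a test of a relative risk of 1.6, and the planned tables carry 95% confidence intervals, which would show imprecision. The background also cites a 3- to 10-fold increase up to 92 days. With 700 events, 10% operated and 5 years, exact power is about 71% at HR 3 and 97% at HR 4.5, so the study may well detect effects of that order.

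Most of this stands, and it limits the seriousness of the point. It does not rescue the sentence: the caveat covers how often surgery occurs, not the change from a fixed to a 3-month exposure.

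A reader might infer that the design's detectable hazard ratio is about 3 to 4.5. The protocol does not support a flat figure: mean follow-up, operations per patient and qualifying events are all missing from it. The upper end is also a Schoenfeld value, and that approximation is unreliable with about 3.5 expected exposed events; the exact calculation reaches 80% power near 3.3.

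A reader might also infer that the 5% was chosen to flatter the result. It was not: in the same fixed comparison, 14.8% would give a minimum relative risk of about 1.34, better than 1.6.

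**Conclusion.** The statement is wrong as written and should be corrected. The arithmetic is sound for a fixed cohort, but that is not the planned analysis. At the protocol's own 10%, with one operation each, 3 to 8 years' mean follow-up and all 700 recurrences counted, power at HR 1.6 is roughly 10 to 23% rather than 80%. The detectable HR is about 2.6 (3 years) to 3.7 (7 to 8 years), higher with fewer qualifying events and lower with more operations.

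The 5% risk next to 14.8% is a secondary point: unexplained and in need of reconciling, but not an outright contradiction, since the 5% has no stated time horizon and the 700 are counted before exclusions.

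It would go too far to conclude that the study cannot answer its question or that a null result is bound to be misread. The error concerns the power claim and the weight a non-significant overall hazard ratio can bear. How sparse surgery-type rows are handled can be left to an analysis plan.

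**What to change.** Delete the sentence claiming 80% power for a relative risk of 1.6. Replace it with a calculation on exposed person-time:

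- Expected events in the windows = event rate × number of operations × 0.25 year, using certain recurrences after the exclusions for cancer and non-linkage.
- Use an exact or binomial method rather than Schoenfeld, because few exposed events are expected.
- Report the detectable hazard ratio and the expected width of its confidence interval over a stated range of operation frequency, mean follow-up and event count, not as one value.
- Reconcile the 5% unexposed risk with 700/4731, or give its time horizon and justify it.

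The cost is a rewrite of section 3b. No new data are needed. The downside is that the stated detectable effect becomes less favourable.
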